### Participant timeline

A timeline of the enrolment, interventions and review of participants in the intervention and control arms is presented in Fig. 2.

**Fig. 2 Fig2:**
[figure not shown]
ORACLE study participant timeline

### Sample size

This is a pilot study designed to assess the feasibility and safety of the ICU oral challenge programme, as well as providing local estimates for subsequent power calculation for future trials.

With regard to the feasibility of penicillin allergy assessment within the ICU, we assume that 9% of all screened patients will report a penicillin allergy as per national data [1], and in an observational study by Moran et al. in Austin Health ICU [6], 200 patients would be expected to be eligible in a 12-month study period. Assuming 50% recruitment and that 85% complete the randomised challenge/observation, this would generate a projected potential pool of 85 eligible participants in 1 year. As such, a total of 80 enrolments and 1:1 randomisation (40 in each arm) are planned.

Whilst the above assumptions may be true (particularly for the primary study site, with an established clinical and research antibiotic allergy service), there are anticipated factors which may limit recruitment. The expected number of 200 eligible patients was calculated from a single tertiary ICU, and the different patient populations of other ICUs may vary the number of eligible patients. Temporary disruptions are expected due to the ongoing SARSCo-V2 pandemic, with altered patient flow through ICUs and investigator availability. Delays in activating study sites may slow recruitment and consistent recruitment may be more challenging at sites with less robust allergy research services.

### Randomisation

Randomisation will be determined by means of an electronically generated allocation sequence using permuted block design, stratified by clinical site. Allocation concealment will be achieved via opaque sealed sequentially numbered envelopes at a single study site (Austin Health). All other study sites will undertake allocation using REDCap (Research Electronic Data Capture).

At Austin Health, generation of the randomisation sequence for the sequentially numbered envelopes will be performed by independent ICU research coordination staff.

The REDCap allocation sequence will be developed and uploaded to REDCap by a trial statistician and will remain concealed prior to allocation.

Allocation will be performed by study investigators (unsealing the opaque envelopes at Austin Health or via the REDCap database randomisation tool at all other sites).

### Blinding

The participant, ICU team and treating clinicians will be blinded to the formal Allergy Assessment Tool result and PEN-FAST score. The participant, ICU team and treating clinicians will not, however, be blinded to the result of eligibility to be randomised (i.e. low risk vs. high risk). The participant, ICU team and treating clinicians will not be blinded to the allocation or outcome of the oral penicillin challenge in participants of the intervention arm.

### Data collection

For all participants, data will be collected during the study by investigators as per the electronic Case Record Form (REDCap). Data to be collected will include basic demographics, medical history, details of the index hospital admission (including diagnosis, critical illness severity, infective episodes and antimicrobial treatment and hospital and ICU length of stay), antimicrobial allergy history, penicillin challenge and/or observation data and any identified antibiotic-associated adverse events during the study period (including serious adverse events). A full list of data points is listed in Additional file 3.

### Statistical methods

Data analysis will be performed on an intention-to-treat basis as well as per protocol. Summary statistics will be used to describe the clinical data and presented as mean ± standard deviation (SD), median with interquartile range (IQR) or percentages as appropriate.

Feasibility and safety outcomes will be reported as percentage with 95% confidence intervals. Logistic regression will be used to compare antibiotic utilisation and mortality between groups. Results will be reported as odds ratios with 95% confidence intervals. Negative binomial regression will be used for comparison of length of stay (reported as incidence rate ratio with 95% CI). Results will be reported according to CONSORT guidelines [17].

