## Background

Patient-reported penicillin allergies result in poor health outcomes for patients and drive inappropriate antibiotic prescribing, antimicrobial resistance and healthcare costs [1–5]. Critically ill patients, such as those in the intensive care unit (ICU), are especially vulnerable to the impact of penicillin allergies [6, 7], yet have been underrepresented in interventional prospective delabelling (i.e. the removal of a patient’s antibiotic allergy history (“label”) via testing or medical record reconciliation [8]) programmes [9]. This impact is magnified, as the prevalence of penicillin allergies is highest in the critical care setting (9–15%) [1], with 50% of these considered low risk and amenable to point-of-care delabelling [3]. Despite the described burden of low-risk penicillin antibiotic allergies being highest in the ICU setting, these have not been addressed in controlled interventional studies.

We recently demonstrated in an Australian ICU that antibiotic allergies are associated with inferior prescribing, in particular the excessive utilisation of vancomycin (aOR 2.04; 95% CI 1.07, 3.86) and inadequate use of narrow spectrum beta-lactams (aOR 0.52; 95% CI 0.29, 0.94) [5]. In a range of observational studies that have included ICU patients, penicillin allergies are associated with the increased use of restricted antibiotics [5].

Our previous work has shown that more than 85% of penicillin allergies can be removed by formal skin prick allergy testing [10], and 96–98% with low-risk allergies can be removed by point-of-care oral challenge (i.e. test dose in non-ICU hospitalised patients) [11, 12]. However, the safety and efficacy of oral challenge in critical care are ill-defined [5]. In a recent systematic review, Moran et al. identified that penicillin allergy testing in the ICU was associated with increased use of narrow-spectrum antibiotics and decreased utilisation of restricted antimicrobials [5]. In addition, in a single-centre study, narrow-spectrum beta-lactams were utilised in 39.5% of ICU patients reporting any antibiotic allergy compared with 58.8% without (*p* = 0.028) [6].

Traditional penicillin allergy skin testing in the ICU has challenges, including the potential for false negatives, resourcing requirements and time pressures [5].

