## Methods/design

### Study objectives

To investigate the feasibility and safety of a direct oral penicillin challenge in adult ICU patients that have a low-risk penicillin allergy (PEN-FAST score < 3). Outcome measures are listed in Table 1 and include the primary outcomes of safety and feasibility of direct oral challenge. Secondary outcomes include proportion of allergy labels removed post-oral challenge, proportion of positive repeat oral challenges, pre- and post-randomisation antimicrobial utilisation, in-hospital and 30-day mortality and length of stay.

**Table 1 Tab1:** Outcome measures

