**Exploratory outcome measures**	
◦ *Proportion of participants in the intervention arm successfully delabelled post oral challenge* ◦ *Proportion of participants in the intervention arm with positive repeat oral challenge (post-ICU discharge)* ◦ *Utilisation of any penicillin during hospital admission* ◦ *Utilisation of any narrow-spectrum beta-lactam during hospital admission* ◦ *Utilisation of vancomycin during hospital admission* ◦ *Utilisation of any restricted antibiotic during hospital admission* ◦ *In-Hhspital and 30-day mortality* ◦ *ICU length of stay and hospital length of stay*	

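### Antibiotic-use outcomes span the whole admission, so use before randomisation counts as an event in either arm; the outcome should start at randomisation, with earlier use as a covariate

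*Protocol article*

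**What the plan says.** The Study objectives list, among the secondary outcomes, "pre- and post-randomisation antimicrobial utilisation, in-hospital and 30-day mortality and length of stay". So the article itself separates antibiotic use before randomisation from use after it.

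Table 1 does not. Under "Exploratory outcome measures" it defines four utilisation measures (any penicillin, any narrow-spectrum beta-lactam, vancomycin, any restricted antibiotic), each over the hospital admission. One of them reads "Utilisation of any narrow-spectrum beta-lactam during hospital admission".

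The Data collection section records details of the index admission, including "critical illness severity, infective episodes and antimicrobial treatment and hospital and ICU length of stay".

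The Statistical methods section states: "Logistic regression will be used to compare antibiotic utilisation and mortality between groups". Results are odds ratios with 95% confidence intervals. The section names no covariate, does not call the models unadjusted, and gives pre-randomisation use no role.

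The Sample size section plans 80 enrolments, 40 per arm. It says the pilot should provide local estimates for power calculations in future trials.

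**The concern.** The challenge can only affect prescribing after randomisation. Patients are enrolled during an ICU stay, and some may already have received the antibiotic class in question. With a whole-admission outcome, every such patient is an event by definition. They raise the event rate equally in both arms in expectation and carry no information about the intervention, so the risk difference and the odds ratio shrink towards no effect. A chance imbalance in prior use also passes straight into the apparent effect. Randomisation is stratified by site only, so nothing in the design balances prior prescribing.

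At stake are the prescribing estimates that the Discussion says will feed larger trials. A diluted estimate would mislead the sample size of such a trial, for example by making it larger than needed.

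A related gap is that pre-randomisation use is collected and may predict later use, but has no stated place in the analysis. Under the Table 1 window it could not be used properly as a covariate, because prior use would determine the outcome.

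**Working it through.** **The plan's own figure.** The article states no power for any between-arm comparison. Its sample size rests on the recruitment pool: 200 × 0.50 × 0.85 = 85, which reproduces the stated 85, with 80 then planned.

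**Inputs for the illustration.**
- n = 40 per arm (Sample size).
- p0 = 0.395 and p1 = 0.588, from the Background: "narrow-spectrum beta-lactams were utilised in 39.5% of ICU patients reporting any antibiotic allergy compared with 58.8% without". This is an observational contrast, not a design assumption. It is borrowed here as the post-randomisation rates in control and intervention.
- Two-sided 5% level: assumed.
- Prior use of the same class, q = 10%, 25% or 50%, equal in both arms: assumed, because the documents give no figure.

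**Step 1: outcome after randomisation.** Power = Φ{[|p1 − p0|√n − 1.96√(2p̄(1 − p̄))] / √[p0(1 − p0) + p1(1 − p1)]}, where p̄ is the mean of p0 and p1.
- Numerator: 0.193 × 6.325 − 1.96 × 0.7070 = −0.165.
- Denominator: √(0.2390 + 0.2423) = 0.694.
- Φ(−0.238) = 0.406, so power is about 41%.

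**Step 2: outcome over the whole admission.** If prior use is unrelated to later use, each arm's event rate becomes q + (1 − q)p, and the risk difference becomes (1 − q) × 0.193.
- q = 10%: 45.6% vs 62.9%, difference 17.4 points, power 34%.
- q = 25%: 54.6% vs 69.1%, difference 14.5 points, power 26%.
- q = 50%: 69.8% vs 79.4%, difference 9.7 points, power 16%.

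**Step 3: sensitivity to the link between prior and later use.** Keep the post-randomisation rates at 39.5% and 58.8%, and let prior use predict later use with odds ratio 8.
- q = 25%: the rates in patients without prior use solve to 27.6% and 48.9% (check: 0.25 × 0.753 + 0.75 × 0.276 = 0.395; 0.25 × 0.884 + 0.75 × 0.489 = 0.588). The whole-admission rates are 0.25 + 0.75 × 0.276 = 45.7% and 0.25 + 0.75 × 0.489 = 61.7%, and power is 30% instead of 26%.
- q = 50%: the rates without prior use are 17.0% and 35.9%. The whole-admission rates are 58.5% and 68.0%, and power is 14% instead of 16%.
- In the limit where every prior user continues the class in either arm, the two outcome definitions coincide and the window costs nothing.

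**Step 4: a covariate without changing the window.** Prior users are all events, so adjusting for prior use leaves only patients without it: 36, 30 or 20 per arm at 39.5% vs 58.8%. Power is 37.1%, 31.8% or 22.6%. The covariate alone recovers only part of the loss, so the window has to change first.

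**Step 5: the covariate once the window is right.** Logistic likelihood-ratio tests were simulated with 40 per arm, 3,000 runs per setting, 50% prior use (assumed) and marginal rates held at 39.5% and 58.8%. Power without and with the covariate:
- covariate odds ratio 1: 42.4% and 41.4%
- 2: 43.6% and 43.6%
- 4: 44.2% and 45.7%
- 8: 43.0% and 49.3%
- 16: 42.9% and 56.6%

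Allowing for further simulations under other settings, the gain is about nil to 3 points at odds ratios of 4 or less, 4 to 8 points at 8, and 8 to 15 points at 16.

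**Step 6: chance imbalance.** With 40 per arm and prior use of 30% to 50% (assumed), exact binomial calculation that ignores site stratification gives a 39% to 43% chance that the arms differ in prior use by at least 10 points.

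**The case against.** The strongest reply has four parts.

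**Silence on covariates is not an omission.** The text is a condensed article, and covariate lists commonly sit in the full protocol or analysis plan. This stands. A reader might infer that the models are fitted by arm only; the Statistical methods section does not say so. The point therefore rests on what is printed: Table 1 fixes a window that conflicts with the distinction made in the Study objectives.

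**These are exploratory outcomes in a pilot sized on recruitment.** Success is judged on feasibility and safety, and no power is claimed for prescribing. This also stands and keeps the severity low. It does not remove the dilution, because the estimates are still meant to inform later trials. A reader might also take the antibiotic models to be the only efficacy comparisons. They are not: mortality and length of stay are compared between groups too.

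**Adjustment does not narrow the interval for the odds ratio.** Correct. In simulation at the same rates, the median standard error of the log odds ratio was 0.46 unadjusted and 0.50, 0.54 and 0.61 adjusted, at covariate odds ratios of 4, 8 and 16. The adjusted odds ratio is conditional and lies further from 1. The precision gain shows in the standardised risk difference and in the test.

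**The size is assumed.** The documents give neither the prevalence of prior use nor its link to later use. All participants carry a penicillin allergy label, so prior penicillin use may be uncommon, and the covariate model may then fail to fit for that class. This stands, and the remedy needs a fallback for sparse classes.

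**Conclusion.** The point holds for the outcome window and, more modestly, for the covariate. As printed, Table 1 turns any use before randomisation into an event that the intervention could not have influenced, although the article elsewhere separates the two periods and collects the data to do so. With the Background rates and 40 per arm, the illustrative loss is from about 41% power to 34%, 26% or 16%. It rests on assumed prior use of 10%, 25% or 50% that is unrelated to later use. With a strong link the loss at 25% prior use is smaller, while at 50% it stays about as large.

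The documents do not support a claim that leaving out the covariate by itself costs a known amount of power. That amount may be nil. Nor do they support judging the trial against a power target, because none is stated. With or without the covariate, power stays well short of 80% across the settings shown, and on these rates 80% would need 105 per arm. This is a low-severity improvement to an exploratory analysis.

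**What to change.** 1. In Table 1, define each of the four utilisation outcomes as use of the class after randomisation, up to hospital discharge.
2. In Statistical methods, state that each is modelled by logistic regression on arm, with one binary covariate: any use of the same class between hospital admission and randomisation.
3. Report from that model the standardised risk difference and the adjusted odds ratio, each with a 95% confidence interval, with the unadjusted figures alongside.
4. State that a class with too few users to fit the model is compared unadjusted.

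If the full protocol or analysis plan already does this, only Table 1 needs to be aligned.

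The cost is a reworded outcome definition and one or two sentences of analysis text. No new data are needed, provided that antimicrobial courses can be dated relative to randomisation, as the pre- and post-randomisation outcome already implies. The model spends one degree of freedom with 80 patients. The adjusted odds ratio is conditional and has a larger standard error on the log scale, which is why the risk difference should be reported with it.

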## Discussion

Penicillin allergy labels are very common in the critical care setting and are associated with significant negative patient and healthcare outcomes [5, 6]. Existing antibiotic allergy assessment and testing programmes have been shown to effectively remove penicillin allergy labels [12]. Point-of-care testing within the ICU has the potential to assess penicillin allergies in a closely monitored environment and reduce the negative effects of allergy labels by promoting β-lactam antimicrobials and limiting exposure to non-preferred alternative antibiotics. However, critically ill patients have been underrepresented in delabelling programmes to date. Furthermore, traditional methods of in vivo allergy assessment (skin testing) have been challenging to implement in critical care patients, with concerns being raised regarding false-negative tests and increased rates of negative histamine control results [9]. This has led some allergy services to focus on the assessment of low-risk penicillin allergy labels in critical illness through direct oral challenge programmes, where skin testing is not required.

Early uncontrolled cohort data provides support for the safety and efficacy of direct oral penicillin challenge in critical illness [13]. However, this study represents the first randomised controlled trial to assess the feasibility, safety and efficacy of a validated point-of-care allergy assessment tool and oral challenge programme in critical illness. Further, through administering repeat challenges post-ICU discharge, this study will provide robust early data on the impact of critical illness on the validity of direct oral challenge. Finally, exploratory data on the impact of oral challenge on antimicrobial prescribing will be collected through detailed electronic medical review and patient telephone review in both the oral challenge and routine care cohorts.

This study will provide feasibility, initial safety and exploratory efficacy data for direct oral challenge for low-risk penicillin allergy in ICU. The findings of this study will be translated into future large-scale, multi-site randomised studies in Australian and international ICUs to more fully explore the impact of oral challenge in ICU on antimicrobial prescribing and patient and health service outcomes and the optimal model for antibiotic allergy assessment in the critical care setting.

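### Scoring vancomycin and restricted-antibiotic use as ever/never over the whole admission counts exposure the challenge cannot alter and misses early stopping

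*Protocol article*

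**What the plan says.** Under Statistical methods: "Logistic regression will be used to compare antibiotic utilisation and mortality between groups". The next sentence fixes the effect measure: "Results will be reported as odds ratios with 95% confidence intervals".

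Table 1 of the protocol lists four utilisation outcomes as exploratory. Two concern drugs the programme hopes to avoid: "Utilisation of vancomycin during hospital admission" and "Utilisation of any restricted antibiotic during hospital admission". Two concern drugs it hopes to promote: "Utilisation of any penicillin during hospital admission" and "Utilisation of any narrow-spectrum beta-lactam during hospital admission". All four share the same window, the whole admission. No measure of quantity, such as days of therapy, is named.

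The Study objectives section describes the outcome differently, as "pre- and post-randomisation antimicrobial utilisation", and calls it secondary.

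The Discussion gives two routes to benefit: more beta-lactam use, and "limiting exposure to non-preferred alternative antibiotics". The Sample size section says the pilot should also supply estimates for powering later trials. The Data collection section lists antimicrobial treatment and length of stay among the recorded data.

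**The concern.** A logistic model needs one yes/no value per patient. With Table 1's window, that value is whether the drug was given at any time in the admission. Participants are ICU inpatients when randomised, so some may already have received vancomycin or another restricted drug. Such a patient scores yes for good. Stopping the drug on the day of a negative challenge and continuing it for two weeks give the same value.

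This does not bias the comparison in favour of one arm, because randomisation balances prior exposure on average. It dilutes the contrast. What is at stake is the planning value of the pilot: a diluted odds ratio for the two avoidance outcomes could mislead the choice of endpoint and the size of the follow-on trial. The feasibility and safety conclusions do not depend on it.

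**Working it through.** **The plan's own figure.** The Sample size section projects 200 × 0.50 × 0.85 = 85 participants in a year, which reproduces, and plans 80 (40 per arm). This is a recruitment projection. No power calculation for antibiotic use lies behind it.

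**Dilution under the whole-admission window.** Let f be the share already exposed before randomisation, and q0 and q1 the shares of the remaining patients who start the drug afterwards (control, intervention).

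- Ever-use = f + (1 − f)q in each arm.
- Risk difference = (1 − f)(q1 − q0).

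The protocol gives neither f nor q, so all values are assumed. Power is for 40 per arm at an assumed two-sided 5%. With q0 = 50% and q1 = 25%:

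| f | Control | Intervention | Difference (points) | Odds ratio | Power |
|---|---|---|---|---|---|
| 0 | 50.0% | 25.0% | 25.0 | 0.33 | 64% |
| 25% | 62.5% | 43.8% | 18.8 | 0.47 | 39% |
| 50% | 75.0% | 62.5% | 12.5 | 0.56 | 22% |
| 75% | 87.5% | 81.3% | 6.3 | 0.62 | 12% |
| 90% | 95.0% | 92.5% | 2.5 | 0.65 | 7% |

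With q0 = 40% and q1 = 20%, the difference falls from 20 points at f = 0 to 10 at f = 50% and 2 at f = 90%; the odds ratios are 0.375, 0.64 and 0.73.

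Two consequences follow from the formula.

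- As f approaches 1, the odds ratio tends to (1 − q0)/(1 − q1), here 0.50/0.75 = 0.67. Avoided new starts therefore keep it away from 1, although the risk difference vanishes.
- If the challenge only shortens courses already running, then q0 = q1, and the odds ratio is exactly 1 however many days are saved.

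**Ever-use against days.** Assume 50% on a restricted drug at randomisation (and no other prior exposure), 5 further days on average, 15% of the rest starting later with the same mean, and 40% switched or spared in the intervention arm.

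- Control ever-use: 0.50 + 0.50 × 0.15 = 57.5%.
- Intervention ever-use, whole admission: 0.50 + 0.50 × 0.15 × 0.60 = 54.5%, odds ratio 0.88.
- Control mean days: 0.50 × 5 + 0.075 × 5 = 2.875.
- Intervention mean days, one further day for switched patients: 0.50 × (0.60 × 5 + 0.40 × 1) + 0.045 × 5 = 1.925, ratio 0.67.
- Intervention mean days, no further day: 0.50 × 0.60 × 5 + 0.225 = 1.725, ratio 0.60.

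**Same inputs, counting only use after randomisation.** Intervention ever-use now depends on whether a switched patient receives another dose.

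- All do: 54.5%, odds ratio 0.88.
- Half do: 44.5%, odds ratio 0.59.
- None do: 0.50 × 0.60 + 0.045 = 34.5%, odds ratio 0.39.

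The day ratio moves far less (0.60 to 0.67) than the odds ratio (0.39 to 0.88).

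**The outcomes that do register a switch.** Start from the 39.5% narrow-spectrum beta-lactam use that the Background cites for ICU patients with an antibiotic allergy, and let a share s of the rest gain such a drug. The rate is 0.395 + 0.605s.

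- s = 32%: 58.8%, odds ratio 2.19.
- s = 50%: 69.8%, odds ratio 3.53.
- s = 75%: 84.9%, odds ratio 8.59.

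**The case against.** The strongest reply is that the four outcomes should be read together. A switch moves a patient from no to yes on the penicillin or narrow-spectrum outcome, and a restricted course never begun also registers. Both points stand. A reader might infer that the pilot will show almost no effect even where prescribing changes, but the protocol does not support that. It fails for two of the four outcomes. For the other two it needs either a high share already exposed or an effect made up mainly of early stopping, and the protocol gives figures for neither.

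A reader might also infer that ever/never use stays insensitive even when counted after randomisation only. That requires nearly every switched patient to receive a further dose. The protocol gives no dosing intervals, and the result swings from 0.88 to 0.39 on that input. Nor is logistic regression itself at fault; it suits a well-defined post-randomisation yes/no.

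Other points carry weight. The outcomes are exploratory. Binary use matches the ICU evidence in the Background. Pilot size limits any measure: 39.5% against 58.8% has about 41% power at 40 per arm, with an expected 95% interval for the odds ratio of 0.89 to 5.34. In simulations over the assumed range, with switched patients given a further day, days of therapy had 9% to 36% power by a rank test, against 5% to 7% for ever-use; the negative binomial model was not itself simulated.

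Finally, the analysis plan and the detailed data list (Additional file 3) are not shown and may set a window or a quantity measure. That would settle the matter in practice, but Table 1 states a window of its own and would still need to agree.

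**Conclusion.** The point holds for vancomycin and restricted antibiotics only. As Table 1 and Statistical methods stand, exposure before randomisation counts as use, and early stopping does not register. The risk difference shrinks by the factor (1 − f), and in the illustrations the odds ratio moves towards 1. The direction follows from the definitions; the size rests on assumed rates, because the protocol gives neither the share already exposed nor the rate of new starts.

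The whole-admission window also sits poorly with the pre- and post-randomisation wording of the Study objectives. A related fault runs the other way: intervention patients receive penicillin as the study challenge. If those doses count, nearly all of them score yes on penicillin use by design, and the odds ratio is inflated or cannot be estimated.

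This is a minor improvement to exploratory outcomes. It matters because the pilot is meant to supply estimates for later trials.

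**What to change.** - Define all four utilisation comparisons on use after randomisation, excluding study challenge doses, and make Table 1 and the Study objectives agree on window and status (exploratory or secondary).
- For vancomycin and restricted antibiotics, add days of therapy after randomisation, compared by negative binomial regression with log days alive in hospital after randomisation as offset. The plan already uses this type of model for length of stay.
- Keep post-randomisation ever/never use alongside, with its odds ratio, and report use before randomisation descriptively by arm.

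The cost is a change of wording and, if the case record form does not already hold them, entry of start and stop dates for each antibiotic. Precision at 40 per arm stays low for every measure, so the results should be presented as estimates with intervals for planning, not as tests of effect.
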